**Methods/Design:**

In this article, we report the design and protocol of a large sample multi-center randomized controlled trial to treat Bell's palsy with prednisolone and/or acupuncture. In total, 1200 patients aged 18 to 75 years within 72 h of onset of acute, unilateral, peripheral facial palsy will be assessed. There are six treatment groups, with four treated according to different path-stages and two not. These patients are randomly assigned to be in one of the following six treatment groups, i.e. 1) placebo prednisolone group, 2) prednisolone group, 3) placebo prednisolone plus acute stage acupuncture group, 4) prednisolone plus acute stage acupuncture group, 5) placebo prednisolone plus resting stage acupuncture group, 6) prednisolone plus resting stage acupuncture group. The primary outcome is the time to complete recovery of facial function, assessed by Sunnybrook system and House-Brackmann scale. The secondary outcomes include the incidence of ipsilateral pain in the early stage of palsy (and the duration of this pain), the proportion of patients with severe pain, the occurrence of synkinesis, facial spasm or contracture, and the severity of residual facial symptoms during the study period.

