## Methods/Design

### Overview

This is a multicentre, randomized, placebo-controlled study (Figure 1). This study has been approved by the ethical committees of Xijing hospital and is registered with ClinicalTrials.gov database (reference no. NCT01201642). The study will be conducted according to the Declaration of Helsinki.

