### Randomization

Patients are to be randomly assigned to one of six treatment groups. A computer-generated allocation sequence (in permuted blocks with a block size of 12) will be created by an operator who is not directly involved with the study. Once created, the allocation sequence will be kept in a secure locked drawer making it inaccessible to all study personnel. Allocation concealment will be achieved using sequentially numbered sealed envelopes which are opaque when held to the light. When a patient is enrolled in the study, an independent researcher will be contacted and asked to give the next numbered envelope to the physician who will make up the medications to be used in the study. The independent researcher will record the patient's details and the number of the envelope assigned to that patient. This procedure ensures that the randomization is not influenced by the researchers taking part in this study.

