### Interventions

Patients will be randomized to one of six treatment arms: placebo prednisolone, prednisolone, placebo prednisolone plus acupuncture (acute stage), prednisolone plus acupuncture (acute stage), placebo prednisolone plus acupuncture (resting stage), or prednisolone plus acupuncture (resting stage) within 72 h after onset of Bell's palsy.

Drug treatment: Prednisolone as 5 mg tablets will be given within 72 h after onset of Bell's palsy as a single dose of 40 mg daily for 5 days; the dose will then be reduced by 10 mg per 5 day, with a total treatment time of 20 days.

Acupuncture therapy: On the basis of previous studies, the acupuncture points used will be Dicang (ST4), Jiache (ST6), Yangbai (GB14), Xiaguan (ST7), Taiyang (EX-HN5), Quanliao (SI18) and Yifeng (TE17) on the affected side, and Hegu (LI4) bilaterally. A qualified acupuncturist will give the acupuncture in every center. For acute stage acupuncture, shallow puncturing will be used at facial acupoints and routine puncturing will be used at other acupoints within 72 h after onset of Bell's palsy. Yifeng (TE17), Hegu (LI4) will be punctured 0.5-1.0 cun, the others will be punctured 0.1-0.3 cun. For resting stage acupuncture, penetrative needling will be used from Dicang (ST4) to Jiache (ST6) and from Taiyang (EX-HN5) to Quanliao (SI18) 2-3 cun, and routine puncturing will be used at other acupoints 7 d after enrolment. Filiform needles (33 - 49.5 mm, 0.32 mm) will be used with moderate stimulation to get an acupuncture sensation, and the needles will be retained for 30 minutes, once a day, five times a week, for a total period of four weeks. The locations of those points are defined in 1993 by the World Health Organization (WHO), Regional Office for the Western Pacific [15].

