Central randomization is used in our trial, which is a strict, complete randomization, and it ensures adequate concealment. During the whole trial, the patients are not aware of which group they are to be assigned to, but they do know they will receive acupuncture treatment at different path-stages. Additionally, this trial is a multicenter randomized controlled study, with six months' follow up, containing a large number of patients. Up to now, our trial is one of the largest randomized controlled trials addressing the effectiveness of prednisolone in combination with staging acupuncture treatment for Bell's palsy.

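### The Discussion says patients do not know their group and will receive acupuncture, but two of six groups get none and no sham is described, so only prednisolone versus placebo can be masked

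*Protocol article*

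**What the plan says.** The last paragraph of the Discussion in the protocol article presents masking among the trial's strengths: "the patients are not aware of which group they are to be assigned to, but they do know they will receive acupuncture treatment". The statement is made for the full duration of the trial, and no exception is made for any group.

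The Abstract (Methods/Design) says otherwise about who is needled: "There are six treatment groups, with four treated according to different path-stages and two not". Its list begins "1) placebo prednisolone group, 2) prednisolone group, 3) placebo prednisolone plus acute stage acupuncture group", so groups 1 and 2 have no acupuncture. Interventions gives the same arms: "Patients will be randomized to one of six treatment arms: placebo prednisolone, prednisolone, placebo prednisolone plus acupuncture (acute stage", and so on. The only placebo named is the tablet.

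Interventions also fixes what patients in groups 3 to 6 will experience: 30-minute sessions with a needle sensation sought, once a day, five times a week, for four weeks. Acute-stage needling begins within 72 h of onset and resting-stage needling 7 days after enrolment.

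Against assessment bias, the Outcomes section names training in facial grading and the use of two scales.

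**The concern.** The Discussion credits the trial with a property that the design cannot have for one of its two factors. A patient knows whether needles were used and when they started.

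This matters because several planned conclusions depend on that factor. One of the two aims in the Abstract is whether prednisolone with staging acupuncture does better than prednisolone alone. Statistics adds an interaction test for the combination. Every contrast of acupuncture with no acupuncture, every contrast between stages, and the interaction compare patients who know which acupuncture level they are in. The primary outcome is facial function on two grading scales, with complete recovery set at a Sunnybrook score of 100. The listed guards, training and two scales, improve consistency of grading but do nothing about knowledge of allocation.

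A reader who took the Discussion at its word would give the acupuncture evidence the weight of a patient-masked comparison.

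**Working it through.** **1. Count the groups.** The Abstract and Interventions define a 2 × 3 layout: drug (placebo, prednisolone) by acupuncture (none, acute stage, resting stage).

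| Acupuncture level | Groups | What the patient sees |
|---|---|---|
| None | 1, 2 | No needling at any time |
| Acute stage | 3, 4 | Needling within 72 h of onset |
| Resting stage | 5, 6 | Needling from 7 days after enrolment |

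Two of six groups have no acupuncture, which reproduces the Abstract's own split of four and two. With 1200 patients in six groups (Patients and enrolment), 1200/6 = 200 per group, so 2 × 200 = 400 patients, one third, receive no needling.

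**2. Test each half of the Discussion sentence.**

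- *Patients will receive acupuncture.* This is untrue for groups 1 and 2.
- *Patients are unaware of their group for the whole trial.* Groups 3 to 6 are scheduled for 5 × 4 = 20 sessions, and the start time separates the two stages. Each patient can narrow six groups to the two within one level. Which of those two remains hidden if the placebo tablet works. The statement is therefore right for the drug and wrong for acupuncture.

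**3. Illustrate what a bias could do.** The document gives no figure for bias, so the shift below is an assumption and is varied. Suppose acupuncture has no effect, true complete recovery is 80% (the treated rate in Patients and enrolment), and the acupuncture arm is recorded d higher. The arms have n = 200, or 200 × 0.85 = 170 after the planned 15% dropout. For a two-sided 0.05 comparison of two proportions:

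P(reject) = Φ((d − 1.96·SE₀)/SE₁) + Φ((−d − 1.96·SE₀)/SE₁)

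with SE₀ = √(p̄(1 − p̄)·2/n), SE₁ = √((p₁(1 − p₁) + p₂(1 − p₂))/n), and p̄ the mean of p₁ and p₂.

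For d = 0.05 and n = 170: p̄ = 0.825, SE₀ = 0.0412, SE₁ = 0.0411. The first term is Φ((0.05 − 0.0808)/0.0411) = Φ(−0.75) = 0.227 and the second is 0.001, giving 22.8%. For n = 200: SE₀ = 0.0380, SE₁ = 0.0379, giving 26.0%.

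| Spurious shift, points of all patients | n = 170 | n = 200 |
|---|---|---|
| 0 | 5% | 5% |
| 1 | 5.6% | 5.7% |
| 2 | 7.6% | 8.0% |
| 5 | 22.8% | 26.0% |

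**4. Judge the top row of that range.** The Background gives, for untreated patients, 71% complete and 84% complete or near-normal recovery, so 84 − 71 = 13% are near-complete. A 5-point shift would need 5 of those 13, or 5/20 = a quarter of the non-recovered at 80% recovery, to be recorded as perfect. If only 5 in 100 of the near-complete were tipped, the shift would be 0.05 × 13 = 0.65 points and the rate about 5.3%. The 5-point case is an upper illustration and not an expectation.

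**The case against.** The best defence is that the sentence is awkward but not false. A patient who sees the needling, or its absence, still does not know whether the tablets are active and so cannot name the group. The clause beginning with 'but' can even be read as conceding that acupuncture is visible. That defence holds for the drug and rightly confines the point to acupuncture. It does not rescue the sentence. The acupuncture level is plain to every patient, the claim covers the whole trial and so cannot mean only the time before allocation, and the promise of acupuncture is untrue for two groups.

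A second defence is that the full protocol may describe a sham. The article, however, says outright that two groups are not given staged treatment and lists them without one. This is a contradiction in the text and not a gap left by condensation.

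A reader might infer three stronger criticisms that the document does not support:

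- **That the design label is wrong.** Overview says "This is a multicentre, randomized, placebo-controlled study (Figure 1"). That is true, because placebo prednisolone exists. It would mislead only if extended to acupuncture, and the article does not extend it.
- **That the drug allocation is disclosed to graders.** Randomization has the independent researcher "give the next numbered envelope to the physician who will make up the medications to be used in the study". It does not say what the envelope shows, which could be a pack code, and nothing says this physician grades facial function. A condensed article may be silent on both.
- **That a third of patients hold a false expectation of acupuncture.** That depends on the patient information, which is not shown.

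Two further reservations stand. The illustration models biased recording of recovery, whereas the sentence concerns what patients know, so correcting the wording would not by itself alter those rates. The illustration also uses a proportion, while the Abstract names time to complete recovery and Statistics plans Cox models.

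**Conclusion.** The sentence is wrong as written and contradicts the Abstract and Interventions. The firm part needs no modelling: two of six groups, about 400 of 1200 patients at equal allocation, receive no acupuncture and no described sham, and all patients can identify their acupuncture level. Patient masking is possible only for prednisolone versus placebo. The contrasts involving acupuncture and its stage, and the prednisolone-by-acupuncture interaction, are open to patients on the acupuncture factor.

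Lack of a sham is a design choice and is not the fault here. The fault is describing the design as if patients were masked to it. The size of any bias is unknown. The rates of about 6%, 8% and 23-26% rest on assumed shifts of 1, 2 and 5 points of all patients at 80% recovery with 170 to 200 per arm, and serve only to show that a modest shift would matter. The prednisolone-versus-placebo contrasts are not affected by this point.

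**What to change.** 1. Replace the Discussion sentence with: *Masking of patients applies to prednisolone versus placebo only; acupuncture versus no acupuncture, and its stage, is open to patients, and two of six groups receive no acupuncture.*
2. Check the patient information and, if it repeats the Discussion wording, make it agree.
3. Report the acupuncture contrasts and the prednisolone-by-acupuncture interaction as comparisons not masked to patients.
4. Unless the full protocol already provides it, state in Outcomes that, among existing staff, neither the acupuncturist nor the person who opens the envelope grades facial function. Training and a second scale do not cover this.

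Cost: a change of wording, some reassignment of tasks at the 17 sites (16 county hospitals and Xijing hospital), and a weaker claim for acupuncture. No sham arm, extra patients, extra assessor or change to any treatment is needed.
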